## Primary Study Endpoints

Reduction in proportion of individuals who are treated with rupatadine who develop DHF (fluid leakage). In our earlier phase 2 study, we found that approximately 25% of hospitalized patients with dengue infection develop fluid leakage when assessed by serial US Scanning. Therefore, the reduction of the proportion of individuals who develop fluid leakage (DHF) will be assessed. As this trial is conducted in an OPD setting, those who are not admitted will considered to only have DF as any patient who is suspected to develop DHF (fluid leakage) will be admitted. By the time of discharge from hospital, as the patient would have recovered at this time point, if the patient had not developed fluid leakage, he/she will considered as not had DHF.

Evidence of plasma leakage will be considered as:

- detection of free fluid in the abdomen or by the presence of a pleural effusion by USScan
- Or by the presence of a rise in haematocrit of >20% of the baseline.

The haematocrit of the patients will be monitored at least three times a day. If the haematocrit at any given time point is >20% of the patients baseline the patient will be considered as having fluid leakage according to the Sri Lanka National Dengue Management guidelines (15). The patients will also be monitored by daily serial ultrasound scans done by the same person using a portable USScanner in the ward. The scans will be recorded and reassessed by a consultant radiologist to ensure accuracy. Presence of fluid in the pleural and peritoneal cavities or a rise in haematocrit of >20% will be considered as evidence of plasma leakage.

Ultrasound scanning will be done in the supine position to assess the peritoneal fluid: in the hepatorenal angle, subdiaphragmatic position, in paracolic gutters and in the pelvis, and patient will be kept seated upright on the examination bed for 2 minutes for all the pleural fluid to gravitate in to costodiaphragmatic recesses and scanned from the back of the chest hands raised up and crossed back of the head, mid and posterior axillary lines and in seated up position.

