# STATISTICS

## Description of Statistical Methods

The interim analysis will be at half way when half the number of patients are recruited. Statistical significance will be calculated for the interim analysis using the

• χ² test for categorical variables in the two groups

• one-way analysis of variance for continuous variables in the two groups

• Kruskal–Wallis for non-parametric continuous variables in the two groups

• Fisher exact test for categorical variables with small sample size in the two groups ( example when the side effects are small in numbers)

• Intention to Treat (ITT) - ITT analysis will be included as this ignores noncompliance, protocol deviations, withdrawal, and anything that happens after randomization

At the end of the trial, the primary endpoint will be the reduction in the number of individuals who develop DHF. And the secondary efficacy endpoints included duration of reduction in stay at hospitals and side effects. Analysis of covariance (ANCOVA) for the primary endpoint and for secondary endpoints will be used as a statistical method in addition to the above basic statistical methods if applicable. This will be supplemented by a repeated measures analysis.

The effect size will also be computed. Standardized mean difference (SMD), which is used for continuous measures such as leakage, and the number needed to treat, which is used for binary outcomes such as side effects in both groups. The SMD will be computed as the difference between drug and placebo divided by their standard deviation:

SMD = (Drug Improvement - Placebo Improvement) / Standard Deviation

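### ANCOVA is named for a yes/no primary endpoint, no test is said to decide at the 0.05 level, and leakage is listed as continuous although it is defined as present or absent

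*Protocol*

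**What the plan says.** **Endpoint.** The protocol's Primary Study Endpoints section compares the proportion of patients who develop DHF. It scores leakage as a finding that is there or not: "Presence of fluid in the pleural and peritoneal cavities or a rise in haematocrit of >20% will be considered as evidence of plasma leakage". Patients who are never admitted count as not having DHF, so every patient ends as a yes or a no. The Description of Statistical Methods agrees: "the primary endpoint will be the reduction in the number of individuals who develop DHF". The Number of Participants section sizes the trial on two proportions, 42.8% and 23.5%.

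**Test.** The Description of Statistical Methods opens its list of basic tests (chi-square, one-way ANOVA, Kruskal–Wallis, Fisher) with "Statistical significance will be calculated for the interim analysis using the". For the end of the trial it says "Analysis of covariance (ANCOVA) for the primary endpoint and for secondary endpoints will be used as a statistical method", and this comes "in addition to the above basic statistical methods if applicable". The next sentence is "This will be supplemented by a repeated measures analysis". The Level of Statistical Significance section gives one level, 0.05.

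**Effect size.** The same section proposes a "Standardized mean difference (SMD), which is used for continuous measures such as leakage", and the number needed to treat for binary outcomes, with side effects as the example. It names no risk difference or risk ratio.

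**The concern.** ANCOVA is a method for continuous outcomes. Naming it for a binary endpoint departs from the two-proportion comparison on which the trial was sized. The chi-square test, which matches that comparison, is introduced for the interim analysis and reaches the final analysis only through a loose clause. Two tests of the same hypothesis can then fall on opposite sides of 0.05, and the protocol does not say which one settles the question.

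The effect-size paragraph adds a second difficulty. It treats leakage as continuous, but no continuous leakage outcome exists among the trial's endpoints. At stake are control of the 5% error rate and a clear statement of how many DHF cases the treatment prevents.

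**Working it through.** **Step 1. Is the endpoint binary in the protocol's own sizing?** Inputs from The Number of Participants: 42.8% and 23.5%, significance level 5%, dropout 10%. Power is given only as 1 − β. I assume 90% and a two-sided test. That section and Table 2 differ on which arm each rate belongs to, which is a separate matter. I take 42.8% as placebo, following Table 2 (ascites 9/21 on placebo, 4/17 on rupatadine).

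n per arm = [1.96·√(2·p̄·q̄) + 1.2816·√(p1q1 + p2q2)]² / (p1 − p2)²

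- p̄ = 0.3315, so √(2 × 0.3315 × 0.6685) = 0.6658
- √(0.428 × 0.572 + 0.235 × 0.765) = √0.4246 = 0.6516
- n = (1.3049 + 0.8351)² / 0.193² = 4.579 / 0.03725 = 122.9, hence 123 per arm
- With 10% dropout: 123 / 0.9 = 136.7, hence 137 per arm and 274 in total

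This is close to the Synopsis figure of 140 per arm, 280 in total. The sizing therefore fits a comparison of two proportions.

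**Step 2. Error rate of each test, and of an open choice.** Trials were simulated with no treatment effect, 126 evaluable patients per arm (140 × 0.9) and one prognostic baseline covariate. Its strength, a log-odds of 1 per SD, is an assumption, because the protocol names no covariate.

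| Analysis | 25% DHF in both arms (20,000 trials) | 42.8% in both arms (8,000 trials) |
|---|---|---|
| Chi-square | 5.1% | 4.9% |
| Fisher | 3.6% | 3.5% |
| ANCOVA on 0/1 | 5.1% | 5.2% |
| Chi-square or ANCOVA significant | 6.9% | 6.9% |

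Allowing Fisher as a third chance adds nothing (still 6.9%). A separate simulation of 4,000 null trials with 280 patients, two assumed covariates and about 25% events gave 5.3% for chi-square, 5.4% for ANCOVA and 7.1% for the better of the two. Two independent 5% tests would give 1 − 0.95² = 9.75%. The overlap between these two tests brings that down to about 7%.

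**Step 3. What one primary comparison of proportions delivers.** At 42.8% against 23.5%, with 126 evaluable per arm:

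- Risk difference 19.3 points; standard error √(0.4246 / 126) = 5.8 points; 95% CI 19.3 ± 11.4, or 7.9 to 30.7
- Risk ratio 23.5 / 42.8 = 0.55
- Number needed to treat 1 / 0.193 = 5.2
- Power: (0.193·√126 − 1.3049) / 0.6516 = 1.322, or 90.7%; with all 140 per arm, 93.3%

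**Step 4. Leakage side by side.** The statistics section gives leakage as an example of a continuous measure. The endpoint section defines it by presence of fluid or by crossing a haematocrit threshold. The secondary endpoints contain no quantity of fluid. As written, the standardized mean difference has no defined leakage outcome to act on.

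**The case against.** Much can be said for the protocol, and most of it stands.

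- **ANCOVA on 0/1 data is not invalid here.** Step 2 shows it holds about 5%, and its treatment coefficient is an adjusted risk difference. A reader might infer that the primary p-value would be wrong. The figures do not support that.
- **The standardized mean difference is never assigned to DHF by name.** By the section's own sorting rule a binary outcome gets the number needed to treat, and side effects are only an example. A reader might infer that the trial's main effect size would be uninterpretable. The text does not go that far. Nor does it help to show that the measure shifts with control risk at a fixed relative reduction, because the risk difference and number needed to treat shift too.
- **Leakage may have meant fluid quantity.** The Background reports effusion height in centimetres and grades of ascites from the earlier trial. That is a fair reading, but this trial defines no such outcome.
- **Repeated measures is described as a supplement and names no outcome.** A reader might count it as a third competing primary analysis. The text does not establish that, so no error rate is computed for it.
- **Covariates and model detail belong in a statistical analysis plan.** Agreed, and their absence is not the point. The protocol positively names ANCOVA for the primary endpoint and places other tests beside it. A plan could cure this only by overriding that sentence.
- **The 7% assumes that either significant result would be accepted.** The protocol does not say so, but it does not rule it out.

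**Conclusion.** The point holds in a limited form. The protocol names a continuous-outcome method for a binary primary endpoint, leaves open whether that method or the chi-square test decides, and classes leakage as continuous against its own definition.

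The cost is about 2 percentage points of extra error (about 7% instead of 5%) if either significant result were accepted. That figure rests on the assumed covariate strength, 126 evaluable patients per arm and DHF rates of 25% to 42.8%. The lack of a stated risk difference or ratio for DHF is a matter of clarity: the number needed to treat can be read as covering DHF, but the protocol should say so. This should be corrected before the data are unblinded. It does not undermine the design or the sample size.

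**What to change.** In Description of Statistical Methods:

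1. Name one primary analysis: the chi-square comparison of the proportion with DHF in all randomised patients at the 0.05 level, reported as a risk difference with 95% CI, together with the risk ratio and number needed to treat.
2. Make any covariate-adjusted analysis of DHF supportive only. Use a binary-outcome model or an adjusted risk difference, with baseline covariates fixed in advance, such as age and baseline platelet count, both already collected.
3. Limit ANCOVA, repeated measures and the standardized mean difference to named continuous outcomes such as platelet count and transaminases. Use ANCOVA only where a baseline value exists. The sleep score, for example, is described at days 14 and 30 with no baseline.
4. If leakage was meant as a quantity, define that outcome (what is measured, when, and how it is summarised) and list it as secondary. Otherwise remove it as an example of a continuous measure.

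The cost is protocol wording and the ethics committee approval that the protocol requires for changes to its statistical plan. For items 1 to 3 no extra patients, visits or measurements are needed.

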The number of adverse events (AE) were similar in those on rupatadine 40mg and on the placebo and all AE completely resolved (Table 1). Two patients (2.98%) in the placebo group developed a SAE, namely acute liver failure. AE such as hepatitis (ALT>250U/L) was more frequent in those on the placebo as 6 (8.9%) patients developed hepatitis when compared to 3 (4.5%) on rupatadine 40mg. Severe thrombocytopenia (<5×10^9^/L) was seen in one patient in the placebo group. However, thromobocyotopenia and hepatitis are known features of dengue and therefore, unlikely to be due to drugs.

|  | Rupatadine 40mg  N=66 | Placebo  N=67 |
| --- | --- | --- |
| Abdominal pain (%) | 17 (25.7) | 21 (31.3) |
| Vomiting (%) | 21 (31.8) | 21 (31.3) |
| Diarrhoea (%) | 27 (40.9) | 24 (35.8) |
| Hepatitis (%) (ALT>250/L) | 3 (4.5) | 6 (8.9) |
| Low platelet counts  <20 ×10^9^/L (%)  20 to 50×10^9^/L (%) | 12 (18.2)  17 (25.7) | 14 (20.9)  21 (31.3) |
| High ALT (>200 U/L) (%) | 9 (13.6) | 12 (17.9) |
| High AST (>200 U/L) (%) | 14 (21.2) | 18 (26.9) |
| Low white cell count  (<1×10^9^/L) (%) | 0 (0) | 0 (0) |

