**Table 1: Adverse events experienced by patients on rupatadine 40mg and placebo**

Although, the overall proportion of patients who developed pleural effusion and ascites was similar in both arms, the mean maximum height of the pleural effusion, was lower throughout the illness in those who were on rupatadine when compared to those on the placebo. We did find a >50% reduction in the mean of the maximum height of the pleural effusion, which was seen on day 8 of the illness in the rupatadine arm (1.7, SD±0.4 cm) when compared to the placebo arm (2.9, SD±1.3 cm). The AST on day 7 of illness was significantly less (p<0.05) in those who were on rupaadine compared to placebo; and rupatadine mildly but significantly reduced thrombocytopenia during the study (Fig 1).

[figure not shown]

**Fig 1:** **Changes in clinical and laboratory parameters in patients on 40mg of rupatadine and placebo**. (A) Height of the pleural effusion was measured by daily ultrasound scan and expressed in time (days) since onset of symptoms. Dotted line represents patients receiving rupatadine (40mg daily, n=66), and solid lines represent those receiving placebo (n=67). (B) Haematocrit was measured daily and expressed as percentage change from the baseline value at presentation. Serum aspartate transaminase levels (C), alanine transaminase (D), and blood platelet counts were measured (E). The bars represent mean and SEM. *P<0.05.

6 (8.9%) patients on the placebo developed significant bleeding, which was considered as any bleeding that was not restricted to the skin. Four of these participants reported per vaginal bleeding (in 3 patients lasting for >3 days), one reported melena and one developed epistaxis. In contrast, 2 (3%) of patients in the rupatadine group developed per vaginal bleeding, which did not last for more than one day. There were no differences in other clinical and laboratory parameters, or the duration of illness in those on the placebo and rupatadine. However, there was a trend for an effect of rupatadine on reducing the overall rise in haematocrits and the rise in ALT.

*Early efficacy of rupatadine*

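### The number needed to treat is the only effect measure planned for side effects; where the arms are similar it is unstable and does not plainly show what excess risk is ruled out (low severity)

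*Protocol*

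**What the plan says.** The Protocol, under Description of Statistical Methods, adds effect sizes to the tests: "The effect size will also be computed". Continuous measures get a standardised mean difference. Binary outcomes get "the number needed to treat, which is used for binary outcomes such as side effects in both groups". The Protocol names no risk difference, risk ratio or odds ratio for binary outcomes.

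The tests in the same section include chi-square and "Fisher exact test for categorical variables with small sample size in the two groups", with side effects given as the example for the latter. The list is introduced for the interim analysis, but the end-of-trial text carries these basic methods forward. Side effects are also a reported endpoint: "the secondary efficacy endpoints included duration of reduction in stay at hospitals and side effects".

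On what to expect, Background and Rationale says of the earlier trial: "The number of adverse events (AE) were similar in those on rupatadine 40mg and on the placebo". Table 1 there gives the counts for 66 rupatadine and 67 placebo patients.

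**The concern.** NNT is one divided by the risk difference. It reads well when the difference is clearly away from zero. Near zero it becomes very large, at zero it does not exist, and a risk-difference interval that spans zero turns into two separate NNT ranges, one for benefit and one for harm, joined through infinity. Side effects are where similar arms are most likely, and the Protocol says they were similar before.

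The question for side effects is how much excess risk the trial can rule out. A p-value does not answer it, and an NNT from near-equal arms answers it only after being turned back into a risk difference. Because the Protocol states this measure itself, a later analysis plan that follows it would inherit the difficulty.

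**Working it through.** **Inputs.** Counts from Protocol Table 1, with 66 rupatadine and 67 placebo patients. Planned size from the Synopsis: 140 per arm. Significance level 0.05, taken as two-sided because sidedness is not stated.

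**Reproducing the Protocol's figures.** Count/66 and count/67 return every Table 1 percentage to within 0.1 point; for example 17/66 = 25.76% (printed 25.7) and 21/67 = 31.34% (printed 31.3).

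**Formulas.** RD = p(rupatadine) - p(placebo), so a positive value means more events on rupatadine. SE = sqrt[p1(1-p1)/66 + p0(1-p0)/67]. Wald 95% interval = RD ± 1.96 SE. NNT = 1/|RD|, labelled benefit or harm by the sign of RD.

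**Example, abdominal pain.** RD = 25.76 - 31.34 = -5.59 points; SE = 7.82; interval -5.59 ± 15.32 = -20.9 to +9.7. NNT = 1/0.0559 = 17.9 (benefit). The reciprocals of the limits are -4.8 and +10.3. Read as an ordinary interval, -4.8 to +10.3 does not contain its own estimate of -17.9.

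| Table 1 row | Rupatadine v placebo | RD, points (Wald 95% interval) | NNT |
|---|---|---|---|
| Abdominal pain | 17 v 21 | -5.6 (-20.9 to 9.7) | 17.9 benefit |
| Vomiting | 21 v 21 | +0.5 (-15.3 to 16.3) | 211 harm |
| Diarrhoea | 27 v 24 | +5.1 (-11.4 to 21.6) | 19.7 harm |
| Hepatitis | 3 v 6 | -4.4 (-12.9 to 4.1) | 22.7 benefit |
| Platelets <20 | 12 v 14 | -2.7 (-16.2 to 10.8) | 36.9 benefit |
| Platelets 20 to 50 | 17 v 21 | -5.6 (-20.9 to 9.7) | 17.9 benefit |
| ALT >200 | 9 v 12 | -4.3 (-16.6 to 8.1) | 23.4 benefit |
| AST >200 | 14 v 18 | -5.7 (-20.1 to 8.8) | 17.7 benefit |
| White cells <1 | 0 v 0 | 0 (Newcombe -5.4 to 5.5) | undefined |

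All eight rows with events have an interval that includes zero (Fisher p from 0.49 to 1.00). Newcombe intervals lead to the same conclusion; hepatitis, the sparsest of the eight, becomes -14.1 to 4.9. The 0 v 0 row has no NNT, but it does have a usable score-type interval.

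**Sensitivity to single patients.** For vomiting, one fewer rupatadine case gives RD = 20/66 - 21/67 = -1.04 points, so 211 (harm) becomes 96 (benefit). For platelets <20, two more rupatadine cases give 14/66 - 14/67 = +0.32 points, so 37 (benefit) becomes 316 (harm). The other rows need more than two patients to change sign.

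**At the planned size.** With the same rates and 140 per arm, all eight intervals still include zero; for example vomiting -10.4 to 11.4 and hepatitis -10.3 to 1.4.

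**If the true rates are equal.** With 140 per arm, NNT = 140/|difference in counts|. It is undefined at equal counts and below 20 when the counts differ by 8 or more. Exact binomial results, for assumed common rates:

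| Assumed rate | Equal counts (no NNT) | NNT below 20, among the rest | NNT 20 or below, among the rest |
|---|---|---|---|
| 30% | 5.2% | 34.6% | 41.8% |
| 10% | 8.0% | 14.6% | 21.1% |
| 5% | 11.0% | 4.5% | 8.3% |

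So for a common side effect with no true difference, an apparently meaningful NNT in one direction or the other is frequent. For a rare one it is not.

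**The case against.** A reader might infer that the safety results would be reported only as figures that cannot be read or bounded. The Protocol does not support that. The effect size is computed in addition to the tests, the tests are built from counts per arm, Table 1 shows the same group reporting adverse events as n (%), and all adverse events are to be recorded. Nothing says that NNT replaces counts.

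A reader might also infer that NNT has no usable value here. That is too strong as well. Seven of the eight rows with events give a finite value of about 18 to 37, and only two change sign with one or two patients. An interval can be written as benefit, through infinity, to harm, and turned back into a risk difference. The Protocol does not itself promise an NNT interval.

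Five of the eight rows (hepatitis, two platelet bands, ALT, AST) are features of dengue that the drug is hoped to reduce, and reducing hepatitis is a specific objective. For those, a number needed to benefit is a conventional choice. The point fits abdominal pain, vomiting and diarrhoea best.

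Finally, the choice of interval method is commonly left to an analysis plan, which is not at hand.

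These arguments reduce the weight of the point but do not remove it. The Protocol itself fixes the measure, offers no other for binary outcomes, and the tests beside it do not give the size of a difference.

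**Conclusion.** The point holds at low severity. The only effect measure stated for side effects suits the expected situation poorly: on the Protocol's own earlier counts, no row with events has an ordinary NNT interval and one row has no NNT. What is lost is a plain statement of the excess risk ruled out.

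The Table 1 results rest on the printed counts and two-sided 95% intervals. The projection to 140 per arm assumes the earlier rates recur. The equal-rate results rest on assumed rates of 30%, 10% and 5% and vary strongly with them, so none should be quoted alone.

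The point does not extend to DHF, although DHF is also binary. With the two proportions in the sample-size section (42.8% and 23.5%), the difference is 19.3 points and the NNT is 1/0.193 = 5.2. At 140 per arm the interval would run from 3.3 to 11.8, which is well behaved if that difference is real.

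**What to change.** In Description of Statistical Methods, change the sentence on binary effect sizes so that, for side effects, the measure is the risk difference (rupatadine minus placebo) with a 95% interval by a score-type method such as Newcombe or Miettinen-Nurminen, shown with n (%) per arm. An NNT or number needed to harm may be added where that interval excludes zero.

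The cost is one sentence. The same counts are used, no further data are needed, and the significance tests, the DHF comparison and the sample size stay as they are.

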## The Number of Participants

This is planned to evaluate rupatidine drug compared to a placebo in reducing the proportion of patients who develop vascular leak (DHF). The response rate of the active control drug, rupatidine in reduction of fluid leakage by Ultra sound scan was found to be 42.8% (p1) and in the standard treatment was 23.5% (p2). The number of participants per group required to detect a difference in the two groups with a significance level of 5% and a power of 1 - β is 280.

[figure not shown]

Given an anticipated dropout rate of 10% , the sample size needed per group is 280.

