# SYNOPSIS

| Trial Title | The efficacy of rupatadine in treating dengue: a randomised, double blinded, placebo controlled trial | |
| --- | --- | --- |
| Short title | Efficacy of rupatadine in dengue | |
| Clinical Phase | Phase 2 | |
| Trial Design | Randomised, double blinded, placebo controlled | |
| Trial Participants | Patients with dengue infection | |
| Planned Sample Size | 280 with 140 each in each study arm | |
| Treatment duration | 5 days | |
| Follow up duration | 30 days of illness | |
| Planned Trial Period | 1 year | |
|  | Objectives | Outcome Measures |
| Primary | To determine the proportions of dengue patients who develop DHF when treated with and without rupatadine | Therefore, the reduction of the proportion of individuals who develop fluid leakage (DHF) will be assessed.  Evidence of plasma leakage: evidence of plasma leakage considered as detection of free fluid in the abdomen or by the presence of a pleural effusion by USScan and/or by the presence of a rise in haematocrit of >20% of the baseline. |
| Secondary | Investigate whether rupatadine treatment leads to a. reduction in complications such as liver failure.  b. Reduction in development of shock:  c. Need of colloids:  d. Need of blood transfusion/s:  e. Duration of the illness.  f. Sleep disturbance | Liver function tests, blood clotting, colloid infusion volumes, blood transfusion volumes, length of acute illness, sleep scores. |
| Investigational Medicinal Product(s) | Rupatadine 40mg | |
| Formulation, Dose, Route of Administration | Four 10mg tablets of rupatadine to be given orally, and placebo | |

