# BACKGROUND AND RATIONALE

Dengue viral infections represent one of the most rapidly emerging mosquito borne infections in the world, spreading to many geographical regions and causing almost 100 million apparent dengue infections each year (1). From 2005 to 2015, although the mortality rates due to many infectious diseases decreased, the deaths due to dengue increased by 48.7%, resulting in an estimated 18,400 deaths in 2015 (2). Although there is now a dengue vaccine, which is licenced to be used in individuals over 9 years of age in several countries, it is only recommended in countries with high rates of dengue seroprevalence, due to its varied efficacy (3). Intense monitoring with meticulous fluid control is currently the only option in the management of acute dengue infection, as specific treatments for dengue are not yet available.

Severe dengue is characterized by clinically detectable vascular leak, which can lead to haemodynamic instability and shock. Vascular leakage is a hallmark of dengue haemorrhagic fever (DHF) and is thought to occur due to endothelial dysfunction(4) resulting in increased vascular permeability. We recently reported that platelet activating factor (PAF) is elevated during acute dengue infection and is an important mediator of vascular leak (5). Therefore, we used rupatadine in a phase 2 trial to determine its efficacy in treating acute dengue, as it had PAF receptor blocking activities. The clinical trial was a phase II, randomized controlled study, initially consisting of three arms, which were rupatadine 10mg, rupatadine 40mg and placebo. This study was carried out at a dedicated dengue management unit in a tertiary care hospital in Colombo District, Sri Lanka (Infections Diseases Hospital) in 2015/6. Patients who had clinical features suggestive of an acute dengue infection, with a duration of illness ≤ 5 days, and who did not show any evidence of vascular leak and also tested positive for dengue NS1 antigen were recruited. An interim analysis was carried out after recruiting half of the number of patients (n=120). At the interim analysis, it was found that 40mg rupatadine was safe in acute dengue, and that 10mg of rupatadine did not seem to show any benefit when compared to the placebo, and so the rupatadine 10mg arm was discontinued.

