17 (25.7%) who were assigned to the rupatadine arm and 21 (31.3%) assigned to the placebo arm were recruited at ≤3 days of illness. The overall duration of illness was significantly less in the early treatment group (p=0.03). Of those who were on rupatadine and treated, only one patient (5.9%), developed a pleural effusion, when compared to 6 (12.2%) of those who were recruited later than 3 days (12.2%) (Table 2), but this did not reach significance. Although the proportion of patients who developed ascites was similar, the severity was less in the early treated group in which only one patient (5.9%) developed moderate ascites compared to nine (18.4%) of those who were recruited late. Of those who were recruited early only one (5.9%) patient was given colloids (dextran) in anticipation of subsequent deterioration, when compared to 5 (10.2%) of those who were recruited later. Only one patient (5.9%) had a rise in had the haematocrit rise >20% at some time during the when compared to 8 (16.3%) in the late treatment group.

|  | **Placebo**  **Recruited ≤ 3 days**  **N=21** | **Rupatadine**  **Recruited ≤3 days**  **N=17** | **P value** |
| --- | --- | --- | --- |
| Pleural effusion by Ultra Sound Scan | 3 (14.3) | 1 (5.9) | NA |
| Ascites by Ultra sound scan | 9 (42.8) | 4 (23.5) | 0.3 |
| Extent of Ascites as measured by US Scan  Mild  Moderate | 5 (23.8)  4 (19.4) | 3 (17.6)  1 (5.9) | NA |
| Duration of illness  Median (IQR)  Mean (SD±) | 7 (6 to 8.5)  7.1 (1.8) | 7 (5.5 to 7)  6.3 (1.5) | 0.2 |
| Haematocrit >20% rise from baseline | 4 (19.4) | 1 (5.9) | 0.3 |
| Low platelet counts  <20,000  20,00 to 50,000 | 5 (23.8 )  7 (33.3) | 2 (11.7)  7 (41.2) | NA |
| High ALT (>200 U/L) | 2 (9.5) | 1 (5.9) | NA |
| High AST (>200 U/L) | 6 (28.5) | 1 (5.9) | NA |

**Table 2: Clinical and laboratory features of patients who were on rupatadine on the placebo who were recruited on ≤ 3 days**

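### The sample-size rates are ascites rates attached to the wrong arms; they are not reconciled with the primary endpoint, the quoted 25% leakage rate or the three stated sample sizes, so the trial's power is unclear

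*Protocol*

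**What the plan says.** Protocol, The Number of Participants, takes its two planning rates from the earlier phase 2 trial and gives the response rate of "rupatidine in reduction of fluid leakage by Ultra sound scan was found to be 42.8% (p1) and in the standard treatment was 23.5% (p2"). It sets a 5% significance level, writes power only as a symbol, allows 10% dropout, and arrives at 280 per group.

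The source is Table 2 in Background and Rationale, whose first data column is placebo (N=21) and second is rupatadine (N=17). The row reads "Ascites by Ultra sound scan | 9 (42.8) | 4 (23.5) | 0.3". The size of this subgroup is given in the text above the table: "17 (25.7%) who were assigned to the rupatadine arm and 21 (31.3%) assigned to the placebo arm were recruited at ≤3 days of illness". On the setting, the Background says: "This study was carried out at a dedicated dengue management unit in a tertiary care hospital in Colombo District". For that trial as a whole it reports that "the overall proportion of patients who developed pleural effusion and ascites was similar in both arms".

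Primary Study Endpoints defines a wider outcome: "Presence of fluid in the pleural and peritoneal cavities or a rise in haematocrit of >20% will be considered as evidence of plasma leakage". The same section states that "approximately 25% of hospitalized patients with dengue infection develop fluid leakage when assessed by serial US Scanning", without naming an arm, and counts patients who are never admitted as not having DHF.

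The planned size is "280 with 140 each in each study arm" in the Synopsis, 262 in total in section 8.4, and 280 per group in The Number of Participants.

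**The concern.** Four things in the sample-size paragraph do not fit the rest of the protocol.

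- **Arms.** Placebo's 42.8% is given to rupatadine and rupatadine's 23.5% to standard treatment. A proportion with fluid has become a response rate.
- **Outcome.** The rates are for ascites alone. The endpoint is peritoneal fluid, pleural effusion or a haematocrit rise above 20%.
- **Event rate.** The endpoint section quotes about 25%, and the paragraph does not say why 42.8% was preferred or how the two relate.
- **Size.** Three different totals are in force.

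What is at stake is how a null result would be read. If the control rate is well below 42.8%, 140 per arm may miss a benefit of the size the investigators hope for. The protocol gives the reader no means of seeing this.

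**Working it through.** **Inputs.** Rates 0.428 and 0.235 and dropout 10% (The Number of Participants); alpha 0.05 (The Level of Statistical Significance); 140 per arm (Synopsis); about 25% leakage (Primary Study Endpoints). Assumed: a two-sided test, and 90% power for the reproduction, since the readable text gives no number.

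**1. Strength of the source.** 9/21 − 4/17 = 0.429 − 0.235 = 0.193. SE = √(0.429×0.571/21 + 0.235×0.765/17) = 0.149. 95% CI = 0.193 ± 1.96×0.149, or −9.9 to 48.6 percentage points. Fisher p = 0.31; the table prints 0.3.

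**2. Reproducing the plan's size.** With p̄ = (0.428 + 0.235)/2 = 0.3315:

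n = [1.96√(2p̄(1−p̄)) + 1.282√(p1(1−p1) + p2(1−p2))]² / (p1−p2)² = [1.96×0.6657 + 1.282×0.6516]² / 0.193² = 123 per arm.

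123/0.9 = 137 per arm, which fits 140 per arm. Unpooled variance gives 134 and a continuity correction 149. Exchanging p1 and p2 changes nothing. One- and two-sided versions, with and without continuity correction, from 80% to 99% power, reach at most 249 after dropout, so none yields 280 per group.

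**3. Power at 140 enrolled, 126 analysed per arm (140×0.9).** Power = Φ{[|p1−p2|√n − 1.96√(2p̄(1−p̄))] / √(p1(1−p1)+p2(1−p2))}.

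For 0.428 v 0.235: (0.193×11.225 − 1.96×0.6657)/0.6516 = 1.32, so power is 90.7%.

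Keeping the relative risk 0.235/0.428 = 0.549 (a 45% reduction), a control rate of 25% becomes 25% v 13.7%: (0.1127×11.225 − 1.96×0.5588)/0.5531 = 0.31, so power is 62.1%.

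| Assumption, 126 analysed per arm | Rates | Power |
|---|---|---|
| As in the sample-size section | 42.8% v 23.5% | 91% |
| 25% is the control rate, same relative risk | 25% v 13.7% | 62% |
| 25% is the control rate, same odds ratio | 25% v 12.0% | 76% |
| 25% is the two-arm average, same relative risk | 32.3% v 17.7% | 76% |
| 25% is the control rate, same 19.3-point difference | 25% v 5.7% | 99% |
| Control 20% (assumed), same relative risk | 20% v 11.0% | 51% |
| Control 15% (assumed), same relative risk | 15% v 8.2% | 39% |

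**4. Dependence on the size.** For 25% v 13.7%: 67% with all 140 analysed (93% for 42.8% v 23.5%); 59% with 118 analysed (262 in total, 131 per arm, less 10%); 89.5% with 252 analysed (280 per group less 10%).

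**5. Detectable difference.** At a 25% control rate and 126 per arm, 80% power needs a fall to about 11.4%, a relative reduction of (25 − 11.4)/25 = 54%.

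**The case against.** The strongest reply is that the arm swap is a wording slip with no effect on N, and that the early-recruited subgroup is the natural planning source because this trial also enrols early cases. Both statements are right. The reply continues that 25% is no better a benchmark: it too comes from inpatients of the earlier trial, which took patients up to day 5 of illness, it rests on ultrasound alone, and no arm is named. That also stands. In any given group of patients the composite cannot be rarer than ascites, so the placebo rate could exceed 42.8%. Outpatient enrolment, with unadmitted patients counted as DF, pushes the other way. The documents give no outpatient rate, so the net direction is unknown.

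Some stronger readings are therefore not supported:

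- A reader might infer that the trial has 62% power instead of a promised 91%. The readable protocol promises no figure; 91% is back-calculated. The 62% needs 126 analysed per arm, 25% taken as the placebo rate and a constant relative reduction.
- A reader might infer that the subgroup was picked after the data were seen. The Background does not say whether it was prespecified.
- A reader might infer that the outpatient rate must be lower than 25%. That is plausible but not documented.

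In the other direction, the 99% for a constant 19.3-point difference gives little comfort: a fall from 25% to 5.7% is a 77% relative reduction, against 45% in the source.

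What the reply does not answer is that the paragraph misreports its own source, plans for a narrower outcome than the one to be tested, ignores the rate quoted in the endpoint section, and states a size that its own inputs do not produce.

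**Conclusion.** The point holds and should be corrected before the sample size is relied on. The reversed labels, the ascites-only source and the three conflicting sizes are plain on the face of the protocol. The effect on power is conditional. At 140 enrolled and 126 analysed per arm, with two-sided alpha of 0.05, power is about 91% at the planning rates. Reading the protocol's 25% as a control or average rate, with the source effect kept as a ratio, it is about 62% to 76%. It is about 51% and 39% at assumed control rates of 20% and 15%. The shortfall largely disappears if 280 per group is really meant, but the stated rates do not lead to that number, and 140 per arm is the likelier intention.

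**What to change.** In The Number of Participants:

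1. Relabel the rates as the proportion with ascites: placebo 42.8% (9/21), rupatadine 23.5% (4/17). Identify the 38-patient source and the width of its confidence interval.
2. State one sample size, per arm and in total, and make the Synopsis, section 8.4 and this section agree.
3. Restate the calculation for the composite primary endpoint, giving the control rate, the assumed effect, the sidedness and the numerical power, and say how 42.8% and 25% relate.
4. Tabulate power at control rates of 42.8%, 25%, 20% and 15%, with the difference detectable at 80% power (at 25% and 126 per arm, a fall to about 11.4%).

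A check of the blinded pooled event rate at the halfway look would be a reasonable addition but is optional.

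The cost is one rewritten paragraph and matching edits in two other places. If 140 per arm is confirmed, no extra patients are needed; the downside is a less favourable stated power. Rewriting does not raise the power, but it lets a null result be read for what it can and cannot exclude.
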